## Methods and design

### Study setting

Zanzibar consists of two major islands, Unguja (also named Zanzibar) and Pemba. They are situated in the Indian Ocean about 40–60 km off the coast of Tanzania and a few degrees south of the equator (Figure 1). In 1964, shortly after independence from the colonial powers, the archipelago and Tanganyika formed the United Republic of Tanzania. Zanzibar as a semiautonomous entity within Tanzania consists of five regions which are subdivided into ten districts, 50 constituencies and 296 communities (Shehias). The main islands cover approximately 2,557 km^2 ^(Unguja: 1,651 km^2^, Pemba 906 km^2^). They are inhabited by a population of approximately 985,000 (in 2002) with Unguja having a share of 63% and Pemba of 37%. The inter-censal annual growth rates (1988–2002) varied from 2.1 to 4.5% [35]. Its mainly Islamic inhabitants are speaking Kiswahili. One-fourth of the population has not received any education and the primary education net enrolment ratio amounts to 77% [36].

**Figure 1 F1:**
[figure not shown]
**Map of Zanzibar with the two main islands**. Courtesy of the University of Texas Libraries. The University of Texas at Austin.

The majority of the population (71%) is having access to piped water while a minority has to rely on drinking water from wells (27%) and other sources like street vendors, rainwater, spring water, and open water courses (2%) [36]. About half of the population (53%) has access to pit latrines, while more than one-fourth has no toilet facility (28%) and 12% – mainly in urban areas – are using a flush toilet.

The top three causes of admission to Zanzibar hospitals in 2007 were malaria (27.4% of all admissions), gastroenteritis (12.7%) and pneumonia (9.9%) [37]. The main causes of death were malaria (18.4%), hypertension (8.5%) and pneumonia (7.9%) with gastroenteritis ranking on fourth place (7.5%). The main sources of help consulted are primary health care units which are situated within four kilometres of households for over 90% of the population. Monthly mean per capita expenditure was TZS21,000 (ca. USD18) in 2004/5 with a 2.1% share for health-related expenditures [36]. Life expectancy at birth has risen from 47 years in 1988 to 57 years in 2002 [35].

#### Target areas

The SEB study will take place in the periurban Shehia of Chumbuni (population estimate: ca. 13,500) in Unguja and the rural Shehia of Mwambe (population estimate: ca. 8,500) in Pemba. These two Shehias represent core areas of the mass vaccination campaign and were selected based on epidemiological data collected from recent cholera outbreaks (Reyburn et al., unpublished data) [13]. The selection of Chumbuni and Mwambe as target areas for the SEB study was therefore based on epidemiological vulnerability criteria (i.e. attack rates) and not on socioeconomic status.

### Methodological framework

The research questions will be answered by using both quantitative and qualitative methods suited for the different stakeholder levels. On levels I to III rapid assessment methods will be used [38,39] while on level IV the cultural epidemiological approach using Explanatory Model Interview Catalogue (EMIC) interviews will be employed [40]. Focus group discussions (FGD) will also be conducted as preparation for EMIC interviews.

#### Level I to III: rapid assessments

Rapid assessments have been utilised to address various health issues including malaria, sexually transmitted diseases, diarrhoeal disease, water and sanitation, and nutrition to name a few. Rapid assessments are methodologically tied to the basic tenets of anthropological ethnographic research which emphasises the use of multiple sources of data to gain various perspectives on social phenomena.

The rapid assessments in this study will provide the meanings and experiences of how community leaders, health care providers and policy makers perceive the importance of cholera as a public health concern and the need and demand for a cholera vaccine. These data will be important for future public health implementation of an oral cholera vaccination programme.

#### Level IV: cultural epidemiology

Cultural epidemiology incorporates qualitative and quantitative methods of health research and uses culturally adapted EMIC interviews to elicit locally valid representations of illness-related experience, meaning and behaviour [41]. Like classical epidemiology, cultural epidemiological research can focus on descriptive, analytical or comparative questions with regard to control of a disease or other public health interests. Analytical studies in cultural epidemiology consider the impact local categories of distress, perceived causes and help seeking – similar to the epidemiological risk factors – are having on clinical or public health outcomes.

A first concept of this research approach was already proposed 20 years ago to the benefit of health planning within the context of diarrhoeal illnesses and ORS promotion [42]. An early validation of this approach was later done in central Thailand when EMIC interviews were used to describe local diarrhoeal illnesses for generating public health policy recommendations [43]. In this study, EMIC interviews will be used to describe the cultural epidemiology of cholera and shigellosis and to estimate determinants of OCV acceptance.

A repeated cross-sectional cultural epidemiological study will be conducted in the two target areas (Figure 2). After a preparatory phase, where focus group discussions will be held, a baseline survey using EMIC interviews (phase 1) will be done in a random sample from each Shehia. After the intervention new samples will be drawn randomly based on the vaccination status. The same instrument will then be used again but with minor changes to account for the post-intervention status of the communities (phase 2).

**Figure 2 F2:**
[figure not shown]
**Outline of the repeated cross-sectional design for household-level study**. Not shown is the preparatory phase taking place before phase 1. F: Female, M: Male.

##### Focus group discussions

Focus group discussions will be used to describe the context of cholera and shigellosis in the target areas. Results from the FGD among community residents will help to guide the planned quantitative research, i.e. the FGD guideline follows the topics and items that will be elicited in the EMIC interviews described below.

##### EMIC interviews

The interview will enquire about the sociocultural context in terms of illness-related experience, meaning and help-seeking behaviour and about topics related to vaccination. Under experience, different aspects of the illness like physical symptoms and psycho-emotional and social problems and also financial issues that can have an impact on patients will be elicited. Under meaning, respondents will be questioned about their views and opinions on why and how they think one can get the illness with regard to various categories of perceived causes including biological, behaviour-related, social and traditional/magico-religious factors. To find out more about sources of help seeking, respondents will be asked to identify and assess all health care providers, i.e. locally available allopathic and traditional sources, patients suffering from cholera or shigellosis will likely consult. The possible options for self-treatment (at home, not at a health-care provider) will also be elicited.

Variables to be elicited will include:

- Sociodemographic factors

- Categories of diarrhoeal illnesses, name of condition

- Perceived severity of cholera and shigellosis episodes

- Perceived vulnerability of cholera and shigellosis

- Illness experience: operationalised as patterns of distress (PD) related to cholera and shigellosis

- Illness meaning: operationalised as perceived causes (PC) related to cholera and shigellosis

- Illness behaviour: operationalised as help seeking (HS) within and outside the household related to cholera and shigellosis

- Stigma (index) of cholera

- Prior episodes of cholera

- Prevention of cholera

- Experience and perception of vaccinations

- Barriers to vaccination (only phase 2)

- Anticipated vaccination status (only phase 1)

- Willingness-to-pay for OCV

- Actual vaccination status, i.e. vaccinated/unvaccinated, not to be elicited but recorded during vaccination campaign

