##### Sample size calculation for EMIC interviews

The following calculations are based on a 95% significance level and 80% power. The prominence means of the different categories of cultural epidemiological variables will be compared in bivariate analyses (by site, gender, anticipated vs. actual vaccination status) and tested for significant differences using the Wilcoxon rank-sum test. To detect a difference of 0.5 between prominence means with equal standard deviations of 1.5, a sample size of 164 for each group is required. The calculation is based on a two-sample t-test assuming a worst-case scenario, i.e. no underlying distribution in the data, which requires that the sample size derived from the t-test (n = 142) be divided by 0.864 which equals 164.4 [44]. Hence, the overall sample size (two groups per phase times two phases) will be 656, with a sample size of 328 per phase.

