##### Instrument

The EMIC interview will be exactly the same as in phase 1 except that a special section will enquire about the experience with the vaccination campaign and reasons against getting vaccinated among both unvaccinated and vaccinated respondents.

The interview teams will attend a second week-long workshop where they can refresh their skills and where the new section of the interview will be explained. A second pilot testing phase will take place to adapt the instrument with regard to the new section.

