##### Sampling

- Sample: adults (≥ 18 years) from the target areas;

- Sampling frame: vaccination campaign data (vaccinated people), census database after exclusion of vaccinated people (unvaccinated people);

- Sampling method: equally stratified random sample among confirmed vaccinated (two doses of OCV) and unvaccinated (one to two doses) people with gender ratio 1:1;

- Exclusion criteria: belonging to stakeholder level I to III, already interviewed in phase 1, member of household already interviewed;

- Sample size: n = 164 per site, n = 328 per phase

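### Phase 2 vaccination status rests on campaign records alone, with no stated check at interview for vaccinated residents left in the unvaccinated stratum

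*Protocol article*

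**What the plan says.** In the variable list under EMIC interviews, the last item is "Actual vaccination status, i.e. vaccinated/unvaccinated, not to be elicited but recorded during vaccination campaign". Status is thus a register variable, and asking the respondent is expressly ruled out.

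Under Level IV: phase 2, Sampling, the frames are "vaccination campaign data (vaccinated people), census database after exclusion of vaccinated people (unvaccinated people"). The two strata are drawn as an "equally stratified random sample among confirmed vaccinated (two doses of OCV) and unvaccinated (one to two doses) people with gender ratio 1:1". Only the vaccinated stratum is described as confirmed.

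Under Level IV: phase 2, Instrument, the interview gains one new part: "a special section will enquire about the experience with the vaccination campaign and reasons against getting vaccinated among both unvaccinated and vaccinated respondents". No question on the respondent's own status is mentioned there, and no rule for an answer that contradicts the register.

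Under Level IV: quantitative data, actual acceptance is one of the two outcome variables for the bivariate screening and the stepwise logistic models. Barriers to vaccination are a separate phase 2 objective.

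**The concern.** The unvaccinated frame is a remainder: everyone in the census who was not identified as vaccinated. Absence from a list does not confirm that a person was not vaccinated. If someone took the vaccine but the campaign entry cannot be linked to the census entry, that person stays in the frame and can be drawn as unvaccinated. For people listed in both sources, this linkage error runs in one direction only. For a given failure rate, its share of the unvaccinated frame grows with coverage, because the remainder shrinks.

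At stake is the phase 2 outcome itself. Vaccination status defines the strata, is the dependent variable in the models of actual acceptance, and decides whose reasons count as those of unvaccinated people in the barrier analysis. If respondents are not asked during the interview, the error cannot readily be measured for them later.

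**Working it through.** **The plan's own figure.** Inputs from Sample size calculation for EMIC interviews: "The following calculations are based on a 95% significance level and 80% power" (read here as two-sided alpha 0.05), a difference of 0.5 and an SD of 1.5.

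- t-test size, normal approximation: n = 2 × (1.960 + 0.842)² × 1.5² / 0.5² = 141.3, rounded up to 142 per group.
- Rank-test inflation: 142 / 0.864 = 164.4, taken as 164.
- Totals: 2 × 164 = 328 per phase and 4 × 164 = 656 overall.

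All four stated figures reproduce. Phase 2 has 328 respondents in equal strata, so 164 are vaccinated and 164 unvaccinated, the size of the planned two-group comparison. Power at the effective size 164 × 0.864 = 141.7 per group is 80%.

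**Effect of contamination.** Let m be the share of the unvaccinated sample that is truly vaccinated. Assume these people score like other vaccinated people. Then:

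- expected difference = 0.5 × (1 − m);
- variance in the unvaccinated group = 1.5² + m(1 − m) × 0.5², averaged with 1.5² for the other group;
- power = Φ(difference / (SD × √(2/141.7)) − 1.96).

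| m | Difference | Power, effective n 141.7 | Power, full n 164 | n per group for 80% power (rank-test basis) |
|---|---|---|---|---|
| 0% | 0.50 | 80.1% | 85.5% | 164 (plan) |
| 2% | 0.49 | 78.5% | 84.1% | 172 |
| 5% | 0.475 | 75.9% | 81.7% | 182 |
| 10% | 0.45 | 71.2% | 77.3% | 204 |
| 20% | 0.40 | 60.8% | 67.2% | 259 |

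The fourth column applies if the rank test loses no efficiency against the t-test. The factor 0.864 is the protocol's worst case.

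**What would produce such an m.** Let c be two-dose coverage and f the share of vaccinees not removed from the census frame. Then m = cf / (cf + 1 − c). Neither c nor f is in the document, so the values below are assumptions chosen to show the range. Power is at effective n with SD 1.5.

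| c | f | m | Power |
|---|---|---|---|
| 30% | 5% | 2.1% | 78% |
| 50% | 2% | 2.0% | 78.5% |
| 50% | 5% | 4.8% | 76% |
| 50% | 10% | 9.1% | 72% |
| 70% | 10% | 18.9% | 62% |
| 80% | 10% | 28.6% | 52% |

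At about 2% contamination the loss is negligible. It becomes serious only when high coverage and a substantial linkage failure occur together.

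**The case against.** Taking status from records is a defensible choice, because it keeps recall and desirability error out of the outcome variable. The document describes no failed match and no poor linkage procedure, and a condensed article may well leave linkage and field verification to the full protocol. The new phase 2 section is put to both strata, so a vaccinated person drawn as unvaccinated might well reveal it there. Relying on self-report instead would bring its own error, possibly related to the attitudes under study.

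Most of this stands, and it rules out several stronger readings that a reader might infer.

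- *That vaccinated people are in fact present in the unvaccinated group.* The document supports only the possibility.
- *That nothing could detect them.* The campaign section might. The text simply assigns it no such use and gives no rule for discordant answers.
- *That every contrast is diluted.* Shrinkage towards zero needs unlinked vaccinees to resemble linked ones. If linkage failure depends on something related to the factors studied, such as mobility or household registration, bias in a single determinant can go in either direction. Comparisons by site, by gender and of anticipated acceptance do not use this variable.

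The objection does not remove the point itself. Ruling out the question is a stated design decision, not a detail lost in condensation, and a frame built by subtraction has no confirmation of its own.

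**Conclusion.** The point holds as an inexpensive improvement to a stated rule, not as a demonstrated error. On the assumption that unlinked vaccinees resemble linked ones, contamination of 2% to 20% lowers the phase 2 power from 80% to between about 78% and 61% on the protocol's worst-case basis. Where the study would fall in that range is unknown, because coverage and match rate are not given. Without that assumption the direction of bias is also unknown, which is a further reason to measure discordance.

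The exposure is confined to phase 2 vaccinated-unvaccinated contrasts, the models of actual acceptance and the barrier analysis.

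A firmer difficulty lies in the same sampling item and needs no assumption. The dose definition given for the unvaccinated stratum overlaps the one given for the vaccinated stratum and, read literally, does not cover people with no dose. Until that is reconciled with the simple vaccinated/unvaccinated split in the EMIC variable list, it is not clear which answers to a dose question would be discordant.

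**What to change.** 1. Reconcile the dose definitions of the two strata in the phase 2 Sampling item with each other and with the EMIC variable list.
2. Keep register status for drawing the sample and for the primary analysis. State the linkage method and the match rate.
3. Replace the clause that rules out eliciting status. At the end of the existing phase 2 campaign section, after all scored items, ask how many doses the respondent took and view any record held.
4. Where answer and register disagree, search the register again. Correct the status only if a campaign record is found, so that self-report alone never moves anyone between groups.
5. Report the discordance rate in each stratum, and add a sensitivity analysis that excludes the respondents who remain discordant.

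The cost is one or two questions in a section that is already planned, a register search for the discordant cases and one further analysis. Self-report carries some error, so the exclusions may remove some correctly classified people. The sensitivity analysis will have slightly smaller groups, and any status corrected from the register leaves the unvaccinated group correspondingly short of 164.

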##### Sample size calculation for EMIC interviews

The following calculations are based on a 95% significance level and 80% power. The prominence means of the different categories of cultural epidemiological variables will be compared in bivariate analyses (by site, gender, anticipated vs. actual vaccination status) and tested for significant differences using the Wilcoxon rank-sum test. To detect a difference of 0.5 between prominence means with equal standard deviations of 1.5, a sample size of 164 for each group is required. The calculation is based on a two-sample t-test assuming a worst-case scenario, i.e. no underlying distribution in the data, which requires that the sample size derived from the t-test (n = 142) be divided by 0.864 which equals 164.4 [44]. Hence, the overall sample size (two groups per phase times two phases) will be 656, with a sample size of 328 per phase.

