### Importance of sociocultural and behavioural research on vaccine introduction

Public health interventions to reduce disease burden must take into account the local realities to achieve a sustainable benefit for the affected populations. Solely relying on prevention or treatment measures that proved to be suitable in a given context does not necessarily make it appropriate for other situations.

Vaccination programmes have suffered a reduced coverage (e.g. rumours about tetanus toxoid causing infertility in Tanzania [16]) or were even brought to a halt because of an ignorance of local realities (e.g. Northern Nigerian resistance to polio vaccination [17,18]). Other interventions, especially when implemented in a top-down approach, experienced the same difficulties [19-21].

To ensure the success of vaccination campaigns, a vaccine should not only be efficacious, relatively trouble-free for patients in its administration and preferably also cost-effective, but it is equally important that implementers consider community-held ideas, fears and individual help-seeking behaviour regarding the infectious disease and the vaccine of interest [22,23].

Infrastructure, logistics, politics, and social and cultural features were identified as significant factors which determine vaccine acceptance and thus the success or failure of immunisation programmes in low-income countries [24-26]. The importance of the social and cultural context on vaccine acceptance was assessed in various recent studies for typhoid fever and shigellosis (e.g. in Asian countries [27-31]). It was reasserted that the importance of the social and cultural context on vaccine introduction has to be studied carefully in order to improve vaccination coverage [32].

Research to improve the health of people needs to include gender issues since they play a crucial role in health and health planning [33]. Gender differences are context-specific and thus require that sociocultural and behavioural research be done to complement clinical or epidemiological research. A recent review on the control of tropical diseases concluded that more detailed data about illness experience, meaning and help-seeking behaviour is needed on the gender level to inform the planning and execution of health interventions [34].

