Socioeconomic features, and cultural beliefs and practices, may vary across and within different sites or populations. And since differences in income, education, neighbourhood, infrastructure, etc. can affect people's health and behaviour regarding risk and relief, it is prudent to include site-specific analyses when doing research on the acceptance of community vaccine interventions.

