##### Sampling

- Sample: adults (≥ 18 years) from both target areas;

- Sampling frame: census and Geographic Information System databases;

- Sampling method: stratified random sample with gender ratio 1:1;

- Exclusion criteria: belonging to stakeholder level I to III;

- Sample size: n = 164 per site, n = 328 per phase

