#### Level IV: quantitative data

Information will be double-entered and cleaned in Epi Info 3.4.3 software. Descriptive statistics and bi- and multivariate analyses will be computed with the statistical analysis programme Stata 10.

Regarding the cholera vignette, the variables related to illness experience (PD), meaning (PC) and help-seeking behaviour (HS) will be coded with a value of two after a spontaneous response, a value of one after a probed response and a value of zero for no response at all to reflect the response style. A value of three will be assigned to the summary variables (i.e. most troubling, most important and most useful). For each category of such a variable, a total prominence will be computed, ranging from zero to five. Thematically similar individual categories will be grouped under specific headings (e.g. "physical symptoms" among PD variables) to enable the analysis of broader concepts of experience, meaning and behaviour. Grouped frequencies will be computed by adding the maximum value based on the response style of each respondent for every single category falling under each group. Calculation of the grouped prominence will follow the same procedure as with the individual variables.

For questions related to the shigellosis vignette, only frequencies of the categories mentioned in relation to illness experience, meaning and help-seeking behaviour will be computed.

Tabulations of the above-mentioned variables will be done after each phase followed by descriptive, bivariate and multivariate analyses to address the research questions.

To test for significant differences (p ≤ 0.05) between two groups, the t-test will be used for normal data and the Wilcoxon rank-sum test for nonparametric data. The Kruskal Wallis test will be used for comparing more than two groups of a nonparametric variable. The Chi^2 ^test and the Fisher's exact test will be applied for comparing two proportions. To compare paired data, i.e. variables between cholera and shigellosis vignettes, the McNemar's Chi^2 ^test, the paired t-test and the paired Wilcoxon test will be used.

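### The gender and vaccination-status tests combine both sites but do not stratify on the sampling strata; this can cost power, and in phase 1 it leaves the anticipated-status comparison open to confounding by site.

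*Protocol article*

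**What the plan says.** All references are to the protocol article.

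- *Sample size calculation for EMIC interviews*: the prominence means "will be compared in bivariate analyses (by site, gender, anticipated vs. actual vaccination status) and tested for significant differences using the Wilcoxon rank-sum test". Each group has 164 people, which gives 328 per phase and 656 in all.
- *Level IV: quantitative data*: for two groups, "the t-test will be used for normal data and the Wilcoxon rank-sum test for nonparametric data". Proportions are compared by Chi-square or Fisher's exact test. No stratified form is named.
- *Level IV: phase 1, Sampling*: "Sampling method: stratified random sample with gender ratio 1:1", with 164 people per site. Anticipated vaccination status is not a stratum.
- *Level IV: phase 2, Sampling*: equal strata of vaccinated and unvaccinated people, gender 1:1, again 164 per site.
- The acceptance models (end of *Level IV: quantitative data*) screen variables at a bivariate p of 0.3 and then run stepwise logistic regression. Site is not forced in, and interactions are not mentioned.
- *Importance of sociocultural and behavioural research on vaccine introduction*: "it is prudent to include site-specific analyses when doing research on the acceptance of community vaccine interventions". The same section says of gender: "Gender differences are context-specific and thus require that sociocultural and behavioural research be done".

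**The concern.** The design fixes the numbers by site and gender, and by status in phase 2, but the named tests set that structure aside. If prominence differs between periurban Unguja and rural Pemba, that difference stays in the error term of the gender and phase 2 status tests. Power that the design has already paid for is then given up.

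The phase 1 comparison by anticipated status has a different problem. Nothing in the sampling balances anticipated status across sites, so an unstratified test can show a site difference as a status difference.

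Finally, the background section favours site-specific analyses, but the named tests contain no step that would show whether a gender or status difference varies by site.

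**Working it through.** **1. The plan's own figure.** Inputs: difference 0.5, SD 1.5 in both groups, "95% significance level and 80% power". I read the first as alpha 0.05, consistent with "To test for significant differences (p ≤ 0.05) between two groups". I assume two-sided testing, which reproduces the stated number.

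- n = 2 × (1.5 × (1.960 + 0.842) / 0.5)² = 141.3, so 142 per group.
- 142 / 0.864 = 164.4, taken as 164; 164 × 4 = 656. All three stated figures reproduce.

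**2. The sites must be combined.** Each site gives 164 per phase. With gender 1:1 there are 82 per site-by-gender cell, so 164 men against 164 women needs both sites. The same holds for phase 2 status, with 82 per site-by-status cell if the equal split is made within each site (the text does not say so outright).

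**3. Power with and without site stratification.** The documents give no site difference D, so I assume a range and take 1.5 as the within-site SD. With equal numbers per site, the pooled SD is √(1.5² + D²/4). The effective n is 164 × 0.864 = 141.7 per group. Power = Φ(0.5 / (SD × √(2/141.7)) − 1.960).

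| Assumed D | Pooled SD | Power, pooled | Power, stratified | n per group for 80%, pooled |
|---|---|---|---|---|
| 0.5 | 1.521 | 79.0% | 80.1% | 169 |
| 1.0 | 1.581 | 75.9% | 80.1% | 182 |
| 1.5 | 1.677 | 70.9% | 80.1% | 205 |

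The last column is rounded up; the same rule gives 165 at D = 0.

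A simulation (3,000 runs, normal scores, 82 per cell) of the pooled rank-sum test against the van Elteren test gave 83.2% vs 83.5%, 81.2% vs 83.7% and 76.7% vs 83.5% at the same three values. Levels are higher because 0.864 is a worst-case factor; the pattern is the same. With no gender difference, the pooled test rejected in 3.8% of runs at D = 1.0 and 1.5% at D = 2.0, against 4.9% and 5.1% for the stratified test. The pooled test is therefore conservative, not inflated.

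**4. Anticipated status in phase 1.** Illustration with assumed values: 60% of one status group and 40% of the other come from the same site, and the sites differ by 1.0. The spurious difference is (0.60 − 0.40) × 1.0 = 0.2, which is 40% of the design difference of 0.5.

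**5. Site in the phase 2 acceptance model.** If each site has 82 vaccinated and 82 unvaccinated people, the bivariate association of site with status is zero by design. Site then cannot pass a p ≤ 0.3 screen, so it enters only if it is fixed in the model.

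**6. Effects that differ by site.** The SE of a difference-in-differences is 1.5 × √(4/82) = 0.331, or 0.356 with the 0.864 factor.

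- Detectable at 80% power: 2.80 × 0.331 = 0.93, or 2.80 × 0.356 = 1.00.
- Power for an interaction of 0.5: 33%, or 29% with the factor.
- Power for 0.5 within one site (82 vs 82): 57%, or 51% with the factor.
- A gender effect of 0.5 at one site and 0 at the other averages 0.25; the pooled test has 29% power.
- Effects of +0.5 and −0.5 leave the pooled test at about 5%. The van Elteren test rejected in 4.2% of simulated runs, so stratifying does not help here.

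**The case against.** The strongest reply is that this is a condensed article. It calls site-specific analyses prudent, makes site a planned comparison for every research question and announces multivariate analyses, so site terms and by-site tables may be in the full plan. That stands for interactions and by-site reporting, where the article is merely silent. It does not dispose of the main point, because the article does name the two-group tests and the ones named are unstratified.

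Second, the power loss depends on an assumed site difference, and 1.5 points is three times the design difference. The SD of 1.5 may also already describe gender groups that span both sites. Pooling would then cost nothing against the planned 80%, and stratifying would only add power: 81.2%, 84.5% and 90.0% at site differences of 0.5, 1.0 and 1.5. This is fair. The loss is modest unless the sites differ by about a point or more.

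Third, the gender test is not biased, because gender is balanced within site. That is right, and it holds for phase 2 status if the split is equal within site. It does not cover anticipated status in phase 1.

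A reader might infer that the plan will hide opposite gender effects on the two islands. The documents do not support that: the background says only that features may vary between sites, and its remark on gender argues for social research alongside clinical work, not for a gender-by-site hypothesis. Nor do they show that the acceptance models are restricted to main effects, or that site will be ignored throughout.

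**Conclusion.** The point holds in a limited form. The named tests for gender and vaccination status do not use the strata in which the sample is drawn, although the group size requires both sites to be combined.

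- For gender, and for phase 2 status if it is split equally within site, the consequence is a conservative test. The power loss is about 1 point at a site difference of 0.5, 4 points at 1.0 and 9 points at 1.5. This assumes a within-site SD of 1.5; the site differences are mine.
- For anticipated status in phase 1, the consequence can be confounding by site. Its size depends on an imbalance that is not known in advance.
- Differing site effects can be masked in a pooled figure. Only by-site estimates or an interaction check would show them, and at 82 per cell such a check is weak below about 0.9 to 1.0 points.

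A site-stratified test does not do materially worse when the sites are alike, so the change is worth making even though its benefit may be small.

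**What to change.** 1. In *Sample size calculation for EMIC interviews* and *Level IV: quantitative data*, stratify the gender and vaccination-status comparisons by site, and by the other sampling strata where relevant: van Elteren's test for prominence and Cochran-Mantel-Haenszel for proportions. Apply site stratification to the phase 1 anticipated-status comparison as well.
2. In the acceptance models, keep site as a fixed term outside the screen and the stepwise selection. In phase 2, if status is split equally within site, the site coefficient reflects the sampling and should not be read as a site effect on uptake.
3. Report gender and status estimates by site with an exploratory site-interaction check. State that it has 80% power only for a difference-in-differences of about 0.9 to 1.0 points, and about 29–33% for 0.5.

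Interaction tests for every variable in the final model are not needed; they would add many low-powered tests.

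The cost is analysis wording and some extra tables. No further interviews are needed.
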